### Power and sample size

Sample size has been calculated to detect minimal significant effects on the variable of physical performance (SPPB) [80, 81]: accepting an alpha risk of 0.05 and a beta risk of 0.20 in a bilateral contrast, 86 individuals are required in order to detect a difference equal to or greater than 1 unit in the SPPB (SD = 2.34). It has been increased the sample size in an additional 20% (loses during follow-up) and 5% (mortality). The resultant sample size is determinate in 114 individuals, therefore 57 individuals per group (intervention and control group).

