**Methods:**

This is a multicentre randomized controlled trial. 114 participants will be randomly allocated to a usual care group or to an intervention group. Inclusion criteria are as follows: ≥ 70 years, ≥ 50 on the Barthel Index, ≥ 20 on MEC-35 who are capable to stand up and walk independently for 10 m. Subjects in the intervention group will add to the activities scheduled for the control group the participation in a 6 months long multicomponent exercise program designed to improve strength, balance and walking retraining. Study assessments will be conducted at baseline and at 3 and 6 months. The primary outcome is change in function assessed by Short Physical Performance Battery and secondary outcomes include other measurements to assess all together the condition of frailty, which includes functionality, sedentary behaviors, cognitive and emotional status and biological markers. The present study has been approved by the Committee on Ethics in Research of the University of the Basque Country (Humans Committee Code M10/2016/105; Biological Samples Committee Code M30/2016/106).

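### The stated inputs give 86 participants per group, but the plan uses 86 as the total, so the stated 80% power is about 50% after the planned losses

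*Protocol article*

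**What the plan says.** The section Power and sample size (protocol article) gives the whole calculation. The error rates are set by "accepting an alpha risk of 0.05 and a beta risk of 0.20 in a bilateral contrast". The result is that "86 individuals are required in order to detect a difference equal to or greater than 1 unit in the SPPB (SD = 2.34"). The number is then increased by 20% for losses to follow-up and 5% for mortality, and the section concludes: "The resultant sample size is determinate in 114 individuals, therefore 57 individuals per group (intervention and control group").

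That 114 covers both groups is confirmed twice. The abstract says that "114 participants will be randomly allocated to a usual care group or to an intervention group", and Trial status sets the end of recruitment at 114 randomised. Allocation is 1:1 (Recruitment and randomization). Outcome measures defines the primary outcome as the difference between intervention and control in SPPB change.

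The section cites no correlation between baseline and follow-up, no covariate adjustment and no gain from repeated measures. It does not say whether 2.34 is the SD of the score or of its change.

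**The concern.** The figure of 86 is what the standard two-group formula returns for one group under these inputs. The plan treats it as the size of the whole trial. If so, the stated beta of 0.20 does not belong to this design.

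One SPPB point is the trial's hypothesis (Objective), and the protocol regards it as clinically relevant (Outcome measures). The Discussion also commits in advance to a strong reading of a null result: decline would be taken to continue despite physical activity, and efforts to prevent disability would be better directed elsewhere. With power near 50%, a programme that truly delivers the target effect would produce that null result about half the time.

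**Working it through.** **Inputs** (all from Power and sample size, except the 1:1 allocation from Recruitment and randomization): two-sided alpha 0.05, so z = 1.96; beta 0.20, so z = 0.8416; difference 1 point; SD 2.34; losses 20% and mortality 5%.

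**Step 1: reproduce 86.** Two independent groups of equal size:

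n per group = 2 × (1.96 + 0.8416)² × 2.34² / 1² = 85.95, rounded up to 86.

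So 86 is reproduced, but per group. The evaluable total is 2 × 86 = 172. The exact t-test calculation gives 87 per group.

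**Step 2: reproduce 114.** 86 / (0.80 × 0.95) = 113.2, rounded up to an even 114. (With a single 25% loss, 86 / 0.75 = 114.7.) The inflation was therefore applied to 86 as the trial total, and 114 / 2 = 57 per group.

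**Step 3: look for a reading in which 86 is a valid total.**
- A one-sided two-group test needs 68 per group, 136 in total. The protocol specifies two-sided.
- The one-sample or paired formula, (1.96 + 0.8416)² × 2.34², gives 42.98, so 43. Doubling it gives 86, but that formula leaves out the variance of the second group and does not apply to a between-group difference.
- For 43 per group to give 80% power, the SD would have to be about 1.66, not 2.34 (normal approximation).

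**Step 4: power for a 1-point difference, SD 2.34, unadjusted two-sample t test** (noncentral t).

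| Evaluable per group | Power | Difference detectable with 80% power |
|---|---|---|
| 43 (after planned losses) | 50.0% | 1.43 |
| 57 (no losses) | 61.9% | 1.24 |
| 86 | 79.6% | about 1.0 |

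The normal approximation gives 50.9%, 62.6% and 80.0%.

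**Step 5: power with baseline-adjusted ANCOVA.** The protocol gives no correlation r between baseline and 6 months, so r is an assumption. If 2.34 is the SD of the score, the residual SD is 2.34 × √(1 − r²). If 2.34 is the SD of change, the SD of the score is 2.34 / √(2(1 − r)), and the residual SD is that value times √(1 − r²).

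| Assumed r | 43 per group, 2.34 = SD of score | 57 per group, 2.34 = SD of score | 43 per group, 2.34 = SD of change |
|---|---|---|---|
| 0.5 | 62% | 74% | 62% |
| 0.6 | 69% | 81% | 59% |
| 0.7 | 78% | 89% | 57% |
| 0.8 | 90% | 96% | 54% |

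Under the first reading, 43 per group reaches 80% at r of about 0.71 to 0.72. Under the second, it does not reach 80% anywhere in this range.

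**Step 6: size needed for 80% power, unadjusted.** 172 / (0.80 × 0.95) = 226.3, about 228 (114 per group). With a single 25% loss, 172 / 0.75 = 229.3, so 230 (115 per group).

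**The case against.** The strongest reply is that 50% is the power of an unadjusted t test, and Statistical considerations does not plan that test for the treatment effect. It plans a repeated-measures ANOVA or Friedman test and, in addition, an ANCOVA with baseline as covariate. If 2.34 is the SD of the score and the correlation exceeds about 0.71, ANCOVA at 43 per group would reach 80%. Use of the 3-month visit might add more. Also, 50% assumes the full planned loss; with complete follow-up the unadjusted figure is 62%.

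This is right as far as it goes: 50% is the power of the calculation as stated, and the power of the final analysis could be higher. It does not rescue the claim. The calculation invokes no adjustment, and its 86 is exactly the unadjusted per-group result. The protocol states no correlation. The primary outcome is framed as change; if 2.34 is the SD of change, ANCOVA gives only 54% to 62%.

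A second reply is that the source of the slip is inferred, since the paired formula doubled also gives 86. That also stands, but either route leaves the between-group comparison with half the participants it needs.

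**Conclusion.** The concern holds. By the protocol's own inputs, 86 is the requirement per group, and the design provides about 43 evaluable per group. Unadjusted power for 1 SPPB point is about 50% after the planned losses and 62% with none, against the stated 80%. With 80% power the trial can detect 1.43 points (43 per group) or 1.24 points (57 per group).

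These figures rest on SD 2.34, two-sided alpha 0.05 and a two-sample comparison, all as stated. Power under baseline adjustment could be higher, but it rests on a correlation and on a meaning of 2.34 that the protocol does not supply. The finding concerns a calculation that is shown in full, so an unseen analysis plan would not change it.

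**What to change.** Correct Power and sample size to 86 per group, 172 evaluable in total. State the formula used and whether 2.34 is the SD of the score or of change. Then restate what 114 randomised (about 43 evaluable per group) provides: about 50% power for 1 point unadjusted, or 80% power for 1.43 points.

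If the sponsor wishes to rely on baseline adjustment, name the baseline-adjusted 6-month ANCOVA as the primary analysis and give its power as a function of the baseline correlation, estimated from the pilot study. This is a helpful addition, but the correction does not depend on it. The Discussion's planned reading of a null result should be softened to match the restated power.

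The cost is protocol and analysis plan wording and a less favourable power statement, with no extra participants. The alternative, keeping 80% power for 1 point without adjustment, means randomising about 228 to 230, twice the present target.

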### Statistical considerations

The IBM SPSS Statistics 23 statistical software package (SPSS, Inc., Chicago, IL) will be used to analyse the data. Intention to treat analyses will be performed. The normal distribution of the data will be evaluated using the Kolmogorov-Smirnov test. Continuous variables will be expressed as mean (SD) when normally distributed and as median with interquartile range (IQR) when not. Categorical variables will be expressed as frequency counts and percentages. Statistical comparisons at baseline will be performed using appropriate statistical tests according to the type and distribution of the data: *t* test or Mann–Whitney *U*-test for continuous variables and Chi-squared test for categorical variables. The intervention-related effects will be performed using appropriate statistical tests according to the type and distribution of the data: an analysis of variance (ANOVA) or Friedman test with repeated measures (0, 3 and 6 months). When a significant F value is obtained, LSD post hoc procedures will be used to evaluate pairwise differences. *p* < 0.05 will be considered to be statistically significant. Furthermore, an analysis of covariance (ANCOVA) will be done to compare the data between intervention and control groups, considering as co-variables baseline measurements, as well as other variables as age or gender.

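### The tests named for the intervention effect, applied as written without imputation, give a complete-case analysis rather than the intention-to-treat analysis promised

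*Protocol article*

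**What the plan says.** All of the analysis text is in the Statistical considerations section of the protocol article.

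- Principle: "Intention to treat analyses will be performed".
- Method for the intervention effect: "an analysis of variance (ANOVA) or Friedman test with repeated measures (0, 3 and 6 months", with the choice depending on the type and distribution of the data.
- Additional comparison: "an analysis of covariance (ANCOVA) will be done to compare the data between intervention and control groups", adjusted for baseline and for variables such as age or gender. No time point is given.
- Software: "The IBM SPSS Statistics 23 statistical software package". No procedure within it is named.

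The section names no mixed model and no imputation. The Power and sample size section starts from a required 86 residents and adds "an additional 20% (loses during follow-up) and 5% (mortality") to reach 114, or 57 per arm.

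**The concern.** Classical repeated-measures ANOVA and the Friedman test need a full row of values for each person. A resident with a missing 3-month or 6-month SPPB is removed from the whole analysis, including the visits that were recorded. The named tests therefore do not by themselves analyse all randomised residents, which is what the same paragraph promises. This rests on methods that the article states, not only on something it leaves out.

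Two things are at stake. First, the 3-month SPPB of a resident lost later says something about the missing 6-month value, and it is thrown away. Second, in nursing-home residents aged 70 or over, loss is likely to follow decline, hospitalisation or death. If an exercise programme changes who is lost, completers in the two arms are no longer comparable, and the estimate can move either way against a target of 1 SPPB point.

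**Working it through.** **Inputs from the documents.** Required number 86, allowances of 20% and 5%, 114 randomised (57 per arm), target 1 point, SD 2.34 (Power and sample size). Visits at 0, 3 and 6 months (Statistical considerations).

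**Step 1: reproduce the plan's inflation.** 86 / (0.80 × 0.95) = 86 / 0.76 = 113.2, rounded up to 114. Simple multiplication, 86 × 1.25 = 107.5, does not reproduce it. The calculation therefore counts on about 86 residents remaining after losses. Whether 86 is the right total for a two-arm comparison is a separate question; nothing here depends on it.

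**Step 2: how many are left out at that allowance.**
- 114 × 0.80 × 0.95 = 86.6 remain, so 114 − 86.6 = 27.4 are absent (24.0%).
- Taking the 86 itself: 114 − 86 = 28 (24.6%).

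**Step 3: whom each named method keeps, without imputation.**

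| Resident | RM ANOVA / Friedman | ANCOVA at 6 months | ANCOVA at 3 months |
|---|---|---|---|
| All three values | kept | kept | kept |
| Month 6 missing | dropped | dropped | kept |
| Only month 3 missing | dropped | kept | dropped |
| Lost before month 3 | dropped | dropped | dropped |

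**Step 4: range of the exclusion.**
- If a further 5% or 10% of those remaining missed only month 3 (assumption), exclusion from the repeated-measures tests would be 1 − 0.76 × 0.95 = 27.8% or 1 − 0.76 × 0.90 = 31.6%.
- If true attrition were 5% or 20%, it would be 114 × 0.05 ≈ 6 or 114 × 0.20 ≈ 23 residents.

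**Step 5: possible bias (illustrative simulation).** There were 4,000 trials of 57 per arm, with SD 2.34 and a true 6-month effect of 1.0. The following are assumptions, not document figures:
- 3-month effect 0.5 and lag-1 correlation 0.8;
- about 24% missing at month 6 and nobody missing at month 3;
- the log-odds of dropout rise with the decline from 0 to 3 months, at the slopes shown.

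| Dropout slope (intervention / control) | Completers, change from baseline | Completers, ANCOVA |
|---|---|---|
| 0.2 or 0 / 0.8 | about 0.65–0.75 | about 0.7–0.8 |
| 0.8 / 0.2 or 0 | about 1.2–1.3 | about 1.1–1.2 |
| 0.4 / 0.4 or 0.8 / 0.8 | about 0.9–1.0 | about 0.9–1.0 |
| 0.3 / 0.5 or 0.5 / 0.3 | about 0.9–1.05 | about 0.9–1.05 |

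A likelihood estimator that also uses the 3-month values gave 0.99 to 1.01. Its standard error was about 0.37, against about 0.42 for completers' change and 0.37 to 0.39 for ANCOVA.

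**The case against.** The strongest reply is that handling of missing data is commonly left to an analysis plan or full protocol, and neither is shown. Imputation followed by ANOVA would fit the article's text. Intention-to-treat is also often used to mean only analysis by allocated arm regardless of attendance, and the named tests do not contradict that. Both points stand. They make the finding conditional on the tests being applied as written.

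Further points that stand:
- The 20% and 5% are a planning margin, not a forecast. The margin is meant to leave the planned 86, so losing 28 residents does not take the trial below its own target count. It protects numbers, not comparability.
- The ANCOVA has no stated time point. Run at 6 months, it would keep residents who miss only month 3, so it would be wrong to say that every named method keeps only those who attend all visits.
- The large biases need strongly different dropout mechanisms between arms. With equal or mildly different mechanisms the bias is small.
- The likelihood estimator's near-zero bias is built into the simulation, where dropout depends only on observed scores. Hospitalisation and death need not follow that rule.

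What the reply does not remove is that the article ties intention-to-treat to tests that cannot use an incomplete row, in a trial that plans for about a quarter of rows to be incomplete.

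**Conclusion.** The point holds in conditional form. Applied without prior imputation, the tests named for the intervention effect are complete-case and fall short of the stated principle. At the plan's own allowance they omit about 27 to 28 of 114 residents (24% to 25%) and discard 3-month scores already collected. Under the assumptions above, bias in a true effect of 1.0 is about 0.2 to 0.35 in either direction when decline-related loss differs strongly between arms. It is roughly 0.1 or less when loss is equal or only mildly different.

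A reader might infer that a quarter of residents will certainly be excluded, that the trial cannot deliver intention-to-treat, or that its result will be materially biased. The documents do not support this. Actual attrition is unknown, imputation is not ruled out, and nothing in the article indicates that loss will differ between arms.

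**What to change.** For SPPB, replace repeated-measures ANOVA or Friedman with a likelihood-based linear mixed model for repeated measures, using all available values from randomised residents analysed by allocated arm. The MIXED procedure in SPSS 23 can fit it.

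- **Terms:** arm, visit, arm × visit, baseline SPPB and centre, with unstructured covariance across visits.
- **Preferred form:** put baseline in the outcome vector, with a common baseline mean for both arms, instead of using it as a covariate. Residents lost before month 3 then stay in the analysis set, although they add little information on the 6-month difference.
- **Primary estimate:** the arm difference at 6 months. Friedman compares visits and gives no between-arm contrast, so it could not supply this.
- **Reporting:** deaths and other losses by arm and visit.
- **Sensitivity:** one analysis that departs from missing at random, for example by shifting the unobserved values by stated amounts, separately by arm.

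If the sponsor prefers to keep ANOVA, the text should state how missing visits are imputed and from which variables.

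The cost is revised wording and slightly more analysis work, with the same software and data. The drawback is reliance on missing at random, which the model does not test and which does not settle how death should be treated; hence the last two items.

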### Outcome measures

The primary outcome measure will be the difference in function between intervention and control group assessed by changes in summary ordinal score on the Short Physical Performance Battery [58] (SPPB). SPPB consists of three tests: balance, gait ability and leg strength. The score for each test is given in categorical modality (0–4) based on run time intervals, and the total score will range from 0 (worst) to 12 points (best). The SPPB has been shown to be a valid instrument for screening frailty and predicting disability, institutionalization and mortality. A total score of less than 10 points indicates frailty and a high risk of disability and falls. 1 point change in the total score has demonstrated to be of clinical relevance [59, 60].

The following parameters will be also recorded: age, gender, socioeconomic situation, marital status, Barthel index [51], MEC-35 [52], Lubben Social Network Scale (LSNS-6) [61], Tilburg Frail index [62], Frailty index [63], and Charlson [64] index. Anthropometric data will include body mass index (BMI) and waist-hip ratio; fat mass percentage will be measured using a portable bio-electrical impedance analyzer (Bodystat BIA Quadscan 4000) [65].

Functional examination will include the following (Table 3): Senior Fitness Test [66], instrumented Timed Up and Go test [67] (iTUG; BTS Biomedical G-WALK triaxial accelerometer and gyroscope), comfortable and fast walking speed [68], bilateral handgrip strength test [69] (Jamar dynamometer), Berg balance test [70], static balance and fall-risk by stabilometer [71] (Biodex Balance System SD), as well as active and sedentary periods during everyday life recorded with an accelerometer (Actigraph GT3X model (Actigraph LLC, Pensacola, FL, USA)) that will be worn on the hip with a belt for a 7 day period. The device will be set to quantify the number of steps taken per day. In line with that, active-period intensities will be classified following the criteria developed by Freedson et al. [72] as light, moderate or vigorous intensity and measured in minutes performed in each intensity.

**Table 3 Tab3:** Functional assessment tests

Test (Reference)	Functions/Parameters	Description

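### Friedman, the non-parametric option named for the intervention effect, compares visits within residents and cannot test intervention against control; the ANCOVA already planned can, but is given no precedence

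*Protocol article*

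**What the plan says.** The protocol article, Outcome measures, defines the primary outcome as a contrast between arms: "The primary outcome measure will be the difference in function between intervention and control group assessed by changes in summary ordinal score" of the SPPB. Each of the three component tests is scored in categories: "The score for each test is given in categorical modality (0–4) based on run time intervals". The sum is an integer: "the total score will range from 0 (worst) to 12 points (best".

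Statistical considerations first sets a distribution check: "The normal distribution of the data will be evaluated using the Kolmogorov-Smirnov test". It then ties the choice of test for the treatment effect to that kind of judgement: "The intervention-related effects will be performed using appropriate statistical tests according to the type and distribution of the data". The tests named are "an analysis of variance (ANOVA) or Friedman test with repeated measures (0, 3 and 6 months". Mann–Whitney, a rank test that does compare two groups, is named in that section only for baseline comparisons.

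The section closes with a further analysis that is not tied to the normality result: "Furthermore, an analysis of covariance (ANCOVA) will be done to compare the data between intervention and control groups", with baseline values among the covariates. No sentence says which of these analyses is primary for the SPPB.

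**The concern.** In a two-arm trial, a test of the intervention effect must contain the arm, either as a main effect on a baseline-adjusted outcome or as an arm-by-time interaction. A repeated-measures ANOVA can carry arm as a between-subject factor. Friedman cannot, because it asks only whether scores differ between visits in one set of subjects.

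There are two ways to apply it here, and neither answers the question. Run on both arms together, it tests for a time trend, so learning of the test or any other shared change would show up as a finding. Run in each arm separately, it invites the conclusion that treatment works because one arm reached significance and the other did not, which is not a comparison of the arms.

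Two features make this branch a realistic one for the primary outcome. The protocol itself calls the score ordinal and lets the type of data steer the choice. An integer score with many ties can also fail a normality test even when the underlying trait is normal. Normality of raw scores is in any case not what ANOVA or ANCOVA requires; those rest on the residuals and, at this sample size, mainly on the behaviour of the estimated means.

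**Working it through.** The plan attaches no figure to this rule, so there is none to reproduce. The check has three parts.

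**1. Friedman contains no arm term.** With n residents and k = 3 visits, let R_j be the sum over residents of the within-resident rank at visit j. Ignoring ties,

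Q = 12/[n·k·(k+1)] · ΣR_j² − 3n(k+1) = (1/n)·ΣR_j² − 12n.

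Arm labels do not enter. Reassigning every resident to the other arm, or shuffling the labels at random, leaves Q unchanged, and the tie correction does not use arm either. This result needs no assumption about the data.

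**2. How often a normality test would send the SPPB there.** Inputs: SD 2.34 (Power and sample size) and range 0–12 (Outcome measures). Assumed: a normal variable with mean 6 to 8, rounded to integers. Critical distances are 1.358/√n for the uncorrected test and 0.886/√n for the version that allows for an estimated mean and SD (Lilliefors).

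| n tested | Uncorrected rejects | Lilliefors rejects |
|---|---|---|
| 57 (one arm) | about 2–3% | about 70% |
| 114 (both arms) | about 24% | over 99% |

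With tabulated p-values and means of 6 to 9, the ranges are 3–7% and 67–85% at n = 57, and 25–53% and 99–100% at n = 114. The protocol does not say which version is meant, whether it is run by arm or pooled, or whether it is applied to scores, changes or residuals.

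**3. What Friedman would report.** Inputs: SD 2.34; 43 per arm, which is half of the 86 given before the allowance for losses; two-sided 5% level. Assumed: baseline mean 7, correlation 0.7 between visits, and half of each 6-month change present at 3 months. ANCOVA is the 6-month score on arm and baseline.

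| Change at 6 months, intervention / control | Pooled Friedman significant | By-arm Friedman significant in intervention arm only | ANCOVA significant |
|---|---|---|---|
| 0 / 0 | about 5% | about 5% | about 5% |
| +0.5 / +0.5 | about 51% | about 20% | about 5% |
| +1 / +1 | about 98% | about 16% | about 5% |
| +0.5 / −0.5 (true difference 1) | about 5% | about 20% | about 77% |

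The ANCOVA figure agrees with a hand calculation. SE ≈ 2.34 × √(1 − 0.7²) × √(2/43) = 2.34 × 0.714 × 0.216 = 0.360, so 1/0.360 = 2.77 and power ≈ Φ(2.77 − 1.96) = 0.79 before the small loss from rounding the score.

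Under other assumptions (57 per arm, correlation 0.8) the pattern is the same. Pooled Friedman is significant in about 82% of trials for a shared 0.5-point gain, about 100% for a shared 1-point gain, and about 5% for +0.5 against −0.5, where ANCOVA reaches about 95%.

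**The case against.** The strongest reply is that the same section already schedules the right analysis. The baseline-adjusted ANCOVA compares the arms and does not depend on the Kolmogorov–Smirnov result, and the primary outcome is itself worded as a between-group difference. A reader might infer from the Friedman clause that the trial may end without any comparison of the arms. The document does not support that, and the point is not made here. What remains is that the repeated-measures test is the one assigned to intervention effects, that ANCOVA follows as an addition, and that nothing says which result counts if they disagree.

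A second reply is that the route into Friedman is uncertain. That stands: with the uncorrected test on one arm, the branch would rarely be entered on distribution alone. The ordinal label could still lead there by data type.

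A third is that the large percentages need a large shared trend. That also stands. A 1-point gain in both arms equals the whole target effect, and the protocol gives no reason to expect it in controls. The 98% is the extreme case. It would be wrong to read any of these figures as the trial's false-positive rate, since they apply only if Friedman is used and its result is read as a treatment effect.

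Finally, an article condenses its plan, and a separate analysis plan may name the primary analysis. That excuses missing detail. It does not excuse naming, for the intervention effect, a test that cannot measure it.

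**Conclusion.** The point holds in this limited form: one of the two tests named for the intervention effect is unsuitable for a two-arm comparison, and the suitable analysis is present without precedence. That Friedman has no arm term is a property of the test and rests on no assumption.

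The size of the harm does rest on assumptions. Under those stated, a shared half-point gain would make pooled Friedman significant in about half of trials with no treatment effect, while a true 1-point difference made up of opposite trends would be detected no more often than chance. How often the branch would be entered cannot be fixed from the document; it runs from about 2% to over 99% depending on the version of the normality test and the sample it is applied to. The rule is worth correcting because it bears on the primary outcome and a valid replacement is already in the plan.

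**What to change.** In Statistical considerations, remove Friedman and the Kolmogorov–Smirnov gate from the analysis of treatment effects. State that the primary test is the between-arm difference in SPPB at 6 months from the baseline-adjusted ANCOVA already planned, or an equivalent linear mixed model with arm, visit and their interaction, used whatever the distribution of the raw scores.

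If a check against distributional assumptions is wanted, name one that keeps the same between-arm contrast, such as rank ANCOVA, a proportional-odds model or a bootstrap confidence interval, and label it a sensitivity analysis. Descriptive summaries may still use mean or median as the data suggest.

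The cost is wording in the protocol and analysis plan. No visit, measurement or sample size changes. It should be settled before outcome data are compared by arm.

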## Methods

### Study design and participants

With the above mentioned objective in mind, it has been designed an experimental multicentre simple randomized study, with random allocation to a usual care group or to an intervention group. Each site will enroll on average 15 subjects. Researchers responsible for data gathering will be blinded for this study. Participants will be recruited from Matia and Caser Residential Care Facilities in 7 long-term nursing homes (San Sebastian, Basque Country, Spain). It is expected that the intervention will take place between October 2016 and June 2017. Study assessments will be conducted by blinded research staff during clinic visits at baseline, as well as at 3 and 6 months from the beginning of the intervention. The CONSORT Statement extension for trials of non-pharmacological interventions and pragmatic intervention trials has been used to design the study and will be used to report it (Fig. 1).

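### The article does not say which visit, which analysis or which F test decides the primary SPPB comparison, although the sample size assumes a single two-sided 5% test

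*Protocol article*

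**What the plan says.** Outcome measures defines the primary outcome: "The primary outcome measure will be the difference in function between intervention and control group assessed by changes in summary ordinal score" on the SPPB. The abstract is no more specific: "The primary outcome is change in function assessed by Short Physical Performance Battery". Neither names a visit, and assessments after baseline are planned "as well as at 3 and 6 months from the beginning of the intervention" (Study design and participants).

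Statistical considerations tests the effects of the intervention by "an analysis of variance (ANOVA) or Friedman test with repeated measures (0, 3 and 6 months"), depending on the distribution of the data. The follow-on rule is "When a significant F value is obtained, LSD post hoc procedures will be used to evaluate pairwise differences". The text then continues: "Furthermore, an analysis of covariance (ANCOVA) will be done to compare the data between intervention and control groups", with baseline values and an open list of further covariates. One threshold, p < 0.05, applies throughout. No sentence ranks the ANOVA and the ANCOVA, gives the visit for the ANCOVA, or says whether the F that opens LSD is for group, time or group-by-time.

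Power and sample size, by contrast, is written for a single two-sided comparison: alpha 0.05, beta 0.20, a difference of 1 SPPB point, SD 2.34.

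**The concern.** Followed as written, the plan offers several results that could each be reported as the answer to the primary question: the group-by-time F, the group F, LSD comparisons after either, and ANCOVA at 3 or at 6 months. If any one of them reaching p < 0.05 could support the claim, the 5% on which the trial was sized is no longer the chance of a false positive claim. An F significant only because both arms change over time could also be read as permission to run unadjusted between-arm comparisons. The routes differ in power as well, so the choice affects the chance of detecting the 1-point effect.

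**Working it through.** **Inputs from the article.** Difference 1 point, SD 2.34, two-sided alpha 0.05, power 80%, 86 evaluable, 114 randomised (57 per arm). Halving 86 gives 43 per arm. **Assumed, because the article gives neither:** the correlation of SPPB between visits (equal correlation 0.6-0.8) and the results that would count as positive.

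**The plan's own figure.** For one two-sided comparison of means, n per arm = 2 × [2.34 × (1.960 + 0.842) / 1]² = 85.95, so 86. The number 86 thus comes from a single test at 0.05. (The formula gives it per arm, whereas the article uses it as the total. That is a separate matter, and it is why 43 and 57 per arm are used below.)

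**Reference for separate tests.** If k tests were independent, the chance of at least one false positive would be 1 − 0.95^k: 9.75% for two and 14.3% for three. The tests here are correlated, so simulation is needed.

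**Simulation with no treatment effect.** Normal data, SD 2.34, visits at 0, 3 and 6 months, 43 per arm:

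| What would count as positive | False-positive rate |
|---|---|
| One pre-named ANCOVA | about 5% |
| 6-month ANCOVA or group-by-time F | about 7-8% |
| ANCOVA at 3 or 6 months | about 9-10% |
| The same, or group-by-time F | about 10-11% |
| The same, or group F | about 14-15% |

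At 57 per arm, with correlations of 0.5-0.85 and an autoregressive pattern of 0.8, the last four rows are 7.5-8.1%, 8.6-9.4%, 10.1-10.9% and 14.2-14.5%.

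**The LSD step.** Under no effect there are two cases.
- Opened only by a significant group-by-time F, between-arm LSD comparisons of change stay near 5%: 4.9-5.6% over all three pairs of visits, and about 4% if only changes from baseline are compared.
- Opened by a time F, they are unprotected. With an assumed decline shared by both arms (0.5 points by month 3, 1 point by month 6; correlation 0.7), the time F was significant in 99.8% of trials. Between-arm comparisons at 3 or 6 months then gave about 8% false positives.

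The Friedman test compares visits within participants, so it does not test the between-arm question.

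**Power, 43 per arm, correlation 0.7, true difference 1 point at 6 months.**
- 6-month ANCOVA: SE = √[(2/43) × 2.34² × (1 − 0.7²)] = 0.360. 1/0.360 = 2.77, so power is about 78%.
- Group-by-time F (2 and 168 df): noncentrality = (43/2) × S / [2.34² × (1 − 0.7)] = 21.5 × S / 1.643, where S is the sum of squared deviations of the effects at 0, 3 and 6 months from their mean.
  - Month-3 effect 0.5: S = 0.5, noncentrality 6.54, power about 62%.
  - Month-3 effect 0 or 1.0: S = 0.667, noncentrality 8.73, power about 75%.

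Simulation agrees: 76-78% for the ANCOVA against 59-75% for the F. The gap is about 17 points in the first case and 2-4 points in the other two.

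**The case against.** **LSD is protected.** It follows only a significant F, and with three visits an LSD gated on the group-by-time F holds its level. This stands. A reader might infer that unadjusted LSD is what breaks the 5%. The documents do not support that, because the ANOVA is introduced as the test of the intervention's effects, which points towards an intervention term. What remains is that the F is not named, and one reading leaves the gate open.

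**The 15% is not a property of the plan.** It requires the group F, averaged over baseline and named nowhere, to count as a win alongside ANCOVA at either visit. This also stands. A reader might infer that the trial runs at 15%. The documents state no such rule, and the defensible statement is a range that starts at 5%.

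**The power loss depends on the assumed trajectory.** This stands: a month-3 effect of 0.5 is the least favourable of the three tried. A general 17-point loss is not shown.

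**Context favours 6 months, and ranking belongs in a SAP.** The programme lasts 6 months, its first half is labelled familiarisation, and the word introducing the ANCOVA can be read as marking a supporting analysis. This makes 6 months the natural choice but does not state it. Nor is the article merely silent: it sets out both analyses, the post hoc step and a common threshold side by side. A SAP that ranks them would settle the matter in substance, but none is shown.

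**Conclusion.** The point holds in limited form. The article leaves open the deciding visit, the deciding analysis and the F that opens LSD, while the sample size rests on one two-sided 0.05 contrast. The text therefore does not secure the 5%. The actual rate lies between 5% and about 15%, and 7-11% covers the intermediate rules. Those figures rest on normal data, assumed visit correlations of 0.6-0.8 and an assumed list of results that would count as positive. The direction is firm, because every rule with more than one route exceeded 5%; the exact size is not. On power, the 6-month ANCOVA was at least as good as the group-by-time F in every trajectory tried with a 1-point effect at 6 months. This should be corrected, but it does not undermine the design.

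**What to change.** - State one primary test: the between-arm difference in SPPB at 6 months, the end of the programme, by ANCOVA adjusted for baseline SPPB, two-sided 0.05.
- Label the 3-month contrast and the repeated-measures ANOVA secondary or supportive. The ANOVA need not be removed.
- Allow LSD between-arm comparisons only after a significant group-by-time F.
- Report within-arm changes descriptively.

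The ANCOVA is already planned, so only wording changes: no extra participants, visits or data. Trial status describes recruitment as still being set up, so the rule can be fixed before outcome data are seen. The small downside is giving up a primary claim at 3 months.
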